### Sociodemographic data

Parents filled out a demographic sheet for themselves and their children, on age, gender, ethnicity, and race. Additional questions for parents included marital and employment status, socioeconomic status and education level. Additional questions for parents to answer about their children included their birth order and health status.

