### Data analysis plan

An intent-to-treat analysis will be used in which all participants are analyzed according to their initial randomized assignment, whether they receive the intervention regularly or not, to preserve the balance of covariates due to randomization and to provide a conservative analysis that does not overestimate intervention effectiveness. Random baseline differences will be accounted for with this approach.

#### Aim 1

To determine the effects of the intervention on weight status, adiposity, health behaviors and self-efficacy, general linear mixed models will be used. Separate random coefficients models will be used to test each outcome for longitudinal differences between the experimental and wait-listed control groups. Advantages of the mixed model approach include its ability to incorporate data from visits that are mistimed as well as certain missing data structures, so that participants who miss one or more visits need not be excluded from the analysis. In addition, random coefficient models accommodate both categorical and continuous covariates.

If a characteristic is found to differ between the groups at baseline, it will be included as a covariate to account for this random imbalance. Additionally, recognizing that certain factors could influence our dependent variables, whether or not they are randomly imbalanced in the two groups, we will control for them as covariates in the models. These variables include asthma, diabetes, low-dose steroids, psychiatric medications (e.g., amitriptyline), cardiac medications (e.g., beta blockers), and recent smoking cessation.

#### Aim 2

The relationships between experimental child changes in weight status, adiposity, health behaviors, and self-efficacy and experimental parent changes in weight status, adiposity, health behaviors, and self-efficacy will also be addressed via the general linear mixed model. Each outcome will be analyzed through a separate random coefficient model. The models will be structured in a fashion similar to that described for Aim 1, but with a different set of predictor variables, in order to examine the associations between improvements in parents and their children. For each model, the children's baseline values for the outcome will be included as a covariate.

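### Aim 1 adds any covariate that happens to differ at baseline, so part of the primary model depends on the observed data, and the plan wrongly credits intention-to-treat with handling baseline differences

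*Protocol article*

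**What the plan says.** All of this is in the protocol article, Data analysis plan, unless another section is named.

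- **Intention-to-treat.** After saying that participants are analysed in their randomized group, the text adds: "Random baseline differences will be accounted for with this approach".
- **Aim 1 model.** "Separate random coefficients models will be used to test each outcome for longitudinal differences between the experimental and wait-listed control groups".
- **Rule (a), triggered by imbalance.** "If a characteristic is found to differ between the groups at baseline, it will be included as a covariate". No criterion for a difference and no list of candidates is given.
- **Rule (b), fixed.** For factors thought to influence the outcomes, the plan says: "whether or not they are randomly imbalanced in the two groups, we will control for them as covariates in the models". It then gives the list: "These variables include asthma, diabetes, low-dose steroids, psychiatric medications (e.g., amitriptyline), cardiac medications (e.g., beta blockers), and recent smoking cessation".
- **Baseline outcome.** It is named as a covariate only under Aim 2: "For each model, the children's baseline values for the outcome will be included as a covariate". The Design section and Table 1 make Time 1 one of four repeated measurements, and the Power analysis section uses measurements from all time points.
- **Ethnicity.** The Exploratory aim section refits the Aim 1 models with ethnicity indicators added as main effects and interactions. They are therefore not in the Aim 1 model as first fitted.

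**The concern.** Under randomization, a baseline difference between arms is chance, and the plan itself calls it random. Its presence does not show that a characteristic predicts the outcome, and its absence does not show that it does not. Under rule (a), the observed data decide which unlisted characteristics enter the primary model. A useful predictor that is balanced stays out, and an irrelevant one that is imbalanced comes in. With no criterion stated, two analysts could reach different models from the same data.

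Taken literally, rule (a) also covers the baseline value of the outcome. Adding it as a covariate while Time 1 is a response would put the same measurement on both sides of one model.

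The intention-to-treat sentence is a separate error. Analysing people as randomized protects the comparison from selective exclusion and switching. It adjusts for nothing, and it may lead a reader to think that chance imbalance has been dealt with.

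**Working it through.** No figure in the document depends on this point, so there is none to reproduce. The sample size cannot be rebuilt either, because no numeric effect size, alpha or target power is given. Four checks follow.

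**1. Which factors are left to rule (a)?** The fixed list holds asthma, diabetes, three medication classes and recent smoking cessation. Age, sex and ethnicity are not named. The list is introduced as examples, so it might be longer in a fuller plan. For ethnicity, however, the Exploratory aim settles the matter, because the indicators are added only on refitting.

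**2. How likely is it that chance triggers the rule?** Assume that a difference means p < 0.05 and that the k tests are independent; neither is in the document. Then P(at least one) = 1 − 0.95^k.

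| k | P(at least one) | Expected number (0.05k) |
|---|---|---|
| 9 | 0.37 | 0.45 |
| 21 | 0.66 | 1.05 |
| 30 | 0.79 | 1.50 |

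**3. What does the rule do to error rates in a simple case?** Simulation: 8,000 runs, 179 per arm (Power analysis section), one normal covariate, one endpoint, independent participants, two-sided alpha 0.05. The true effect of 0.3 SD and the covariate-outcome correlations are assumed.

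| Correlation | Type I error, conditional rule | Power, unadjusted | Power, conditional rule | Power, always adjusted |
|---|---|---|---|---|
| 0.3 | 0.042 | 0.81 | 0.82 | 0.84 |
| 0.5 | 0.043 | 0.81 | 0.82 | 0.90 |
| 0.7 | 0.037 | 0.80 | 0.82 | 0.98 |

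The Monte Carlo standard error at 0.05 is √(0.05 × 0.95 / 8000) = 0.0024. The conditional rule is conservative and forgoes most of the gain from adjustment.

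**4. Does that power loss carry over to the planned model?** Not as it stands, for two reasons.

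- *The test is longitudinal.* Let T hold an intercept and time. Let S0 be the within-person covariance after adjusting for a covariate that shifts the outcome level equally at every visit (correlation r). Without adjustment the covariance is S = S0 + r²·11′. Because the vector 1 is a column of T, (T′S⁻¹T)⁻¹ = (T′S0⁻¹T)⁻¹ + r²·e₁e₁′, where e₁ = (1, 0)′. Only the intercept variance changes, so the variance of the group-by-time slope is the same. Numerically, the standard error of the slope difference is √(2·[(T′S⁻¹T)⁻¹]₂₂/179). I used visits at 0, 0.25, 1 and 1.5 years, outcome SD 1, and correlation 0.90 or 0.84 between adjacent visits (Power analysis section). It is 0.0485 and 0.0597 respectively, with or without a covariate of r = 0.5 or 0.7. A covariate that predicts change could still matter, but the document says nothing on that.
- *Correlations of 0.5 to 0.7 are not supported for ethnicity.* From Tables 2 and 3, parent BMI means are 38.4, 36.3 and 32.8 with shares 0.63, 0.32 and 0.05. The weighted mean is 37.45. The between-group variance is 0.63(0.95)² + 0.32(1.15)² + 0.05(4.65)² ≈ 2.07. Against 8.4² = 70.56 that is 2.9%, a correlation of about 0.17. For child BMI percentile (95.5, 94.0, 95.2; SD 6.4), the same steps give 0.48/40.96 = 1.2%, about 0.11. Both concern baseline level, not change.

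**The case against.** The strongest reply is that the plan already controls for influential factors regardless of balance, in the sentence right after the disputed rule. That stands for the listed conditions and medications. It would be wrong to say that the Aim 1 model simply ignores balanced predictors. It does not cover ethnicity, and as written it does not name age or sex. The child primary outcome is already age- and gender-specific, which weakens the case for those two in that model.

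Stronger readings that a reader might infer are not supported:

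- *Inflated false positives.* Under a mechanical 5% rule the simulated size is below nominal.
- *A changed estimand.* In a linear model, adjusting for a baseline covariate does not alter the mean difference being estimated.
- *A power loss of 8 to 15 points.* That belongs to a single-endpoint model with assumed correlations of 0.5 to 0.7, and check 4 shows why it does not transfer.
- *Bias from covariates measured after assignment.* The plan does not date the listed conditions and medications, but nothing says that they are taken during follow-up. The Sample section describes an entry history and physical examination, and the demographic sheet asks about the child's health status.
- *Baseline outcome used twice.* The rule permits this on a literal reading, but the plan does not say that it will be done.

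A fuller analysis plan may list more covariates. It could not cure the imbalance rule or the intention-to-treat sentence without reversing what the article states.

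**Conclusion.** The concern holds in limited form, as a should-fix. Part of the Aim 1 covariate set is left to observed baseline imbalance with no criterion, and intention-to-treat is credited with something that it does not do. Both follow from the text alone. If 5% tests on 9 to 30 independent characteristics were used, the chance that at least one covariate entered by luck would be 37% to 79%; those inputs are assumptions. The consequence is a data-dependent model and possible loss of precision. The size of that loss in the random coefficients model cannot be derived from the document. It could be nil for covariates related only to outcome level.

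**What to change.** - Delete the rule that adds characteristics because they differ at baseline, and keep baseline comparisons descriptive.
- Prespecify one covariate set for each model on prognostic grounds, from variables already collected at baseline: for example age, sex and ethnicity, plus the listed conditions and medications as recorded at baseline or entry.
- State that the baseline outcome is used once, either as a response or as a covariate.
- Remove the sentence crediting intention-to-treat with accounting for baseline differences, or reword it to say that participants are analysed in the arm to which they were assigned.

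The cost is wording, settled before the comparative analysis, and a few model degrees of freedom out of 358 children or 358 parents. Age, sex and ethnicity are on the demographic sheet. That the entry history captured every listed condition and medication should be confirmed.

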#### Exploratory aim

To determine whether African American, non-Hispanic white, and bilingual Hispanic children and parents in the experimental group benefit differentially from the intervention, two indicator variables for African American and Hispanic children and adults, respectively, will be created, and non-Hispanic whites will serve as the referent group. The models described above for Aim 1 will be refitted, with these indicators added as main effect terms. Additionally, pairwise interaction terms between the intervention indicator and each of these ethnic indicators will be added to the models to assess the degree to which the impact of the intervention differs among these three ethnicities.

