## Aims

The first aim of the trial is to examine the effects of a two-phased intervention on weight status, adiposity, nutrition and exercise health behaviors, and self-efficacy in overweight or obese 2^nd^, 3^rd^, and 4^th ^grade children and their overweight or obese parents. The primary outcome in children is stabilization of the BMI percentile trajectory from baseline to 18 months. The primary outcome in parents is a decrease in BMI from baseline to 18 months. Secondary outcomes for both children and parents include improvements in adiposity, nutrition and exercise health behaviors, and self-efficacy from baseline to 18 months. A secondary aim of the trial is to examine in the experimental group the relationships between parent's and children's changes in weight status, adiposity, nutrition and exercise health behaviors, and self-efficacy. Finally, an exploratory aim is to determine whether African American, non-Hispanic white and bilingual Hispanic children and parents in the experimental group benefit differently from the intervention in terms of weight status, adiposity, health behaviors, and self-efficacy.

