### Sample characteristics

Baseline characteristics of parents and children are summarized in Table 2. The mean age of the parents was 36.7 years and the great majority were female (93%). Over half (63%) of the parents and children were African American, 32% were non-Hispanic white, and 5% bilingual Hispanic. The mean age of the children was 8.6 years and the majority (56%) was also female.

**Table 2 T2:** Demographic Characteristics of Parents and Children

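### The exploratory ethnicity analysis names only arm-by-ethnicity terms, which compare levels with baseline included, although the trial defines benefit as change over time

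*Protocol article*

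**What the plan says.** Under Exploratory aim, the article builds on the main models: "The models described above for Aim 1 will be refitted, with these indicators added as main effect terms". It then states that "pairwise interaction terms between the intervention indicator and each of these ethnic indicators will be added to the models", and gives the purpose as "to assess the degree to which the impact of the intervention differs among these three ethnicities". The two indicators are African American and Hispanic, with non-Hispanic white as the reference. Neither ethnicity-by-time nor arm-by-ethnicity-by-time is mentioned.

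The models being refitted are described under Data analysis plan, Aim 1: "Separate random coefficients models will be used to test each outcome for longitudinal differences between the experimental and wait-listed control groups". Their fixed effects are not written out.

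The Aims section defines what counts as benefit. For children: "The primary outcome in children is stabilization of the BMI percentile trajectory from baseline to 18 months". For parents: "The primary outcome in parents is a decrease in BMI from baseline to 18 months". Both are statements about change.

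A baseline value of the outcome as covariate appears only under Aim 2: "For each model, the children's baseline values for the outcome will be included as a covariate". On group sizes, Sample characteristics reports that 63% of participants were African American, "32% were non-Hispanic white, and 5% bilingual Hispanic".

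**The concern.** In a longitudinal model whose response includes baseline, an arm-by-ethnicity term with no time in it moves the fitted curve up or down by the same amount at every visit. The fitted effect of the intervention on change is then the same in all three ethnic groups by construction, although differences in that effect are what the aim asks about.

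Two errors could follow. A chance baseline difference between arms within one ethnic group could be reported as differential benefit. A real difference in change could be missed, because the named coefficient picks up only part of it and carries the full between-person variation in level.

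**Working it through.** The article gives no figure for this interaction, so there is none to reproduce. The check is of model structure first, then size.

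**Inputs from the article.** 179 pairs per arm (Power analysis). Ethnic mix 63/32/5% (Sample characteristics), giving 0.63 × 179 ≈ 113, 0.32 × 179 ≈ 57 and 0.05 × 179 ≈ 9 per arm. SD 8.4 for parents' BMI and 6.4 for child BMI percentile (Table 3). Autoregressive parameters 0.99 and 0.90 (Power analysis). Visits at 0, 3, 12 and 18 months (Design).

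**Assumptions.** Two-sided 5% test, no dropout, no cluster effect, equal ethnic mix in both arms, autoregressive parameter applied per visit step. D is the difference between African American and white participants in the 18-month intervention effect.

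**1. Structure.** Let A be arm, E an ethnicity indicator, and t time scaled to 1 at 18 months. As written:

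mean = b0 + b1·t + b2·A + b3·A·t + g·E + d·A·E

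The arm contrast of change from baseline to 18 months is b3 whether E is 0 or 1, so its difference between ethnic groups is 0 whatever d is. The coefficient d is the ethnic difference in the arm contrast at every t, including t = 0. If E·t and A·E·t (coefficient θ) are added, the difference in change is θ.

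**2. Level gap only.** With a gap of 2.0 present from baseline and no differential change, generalized least squares gives an arm-by-ethnicity coefficient of 2.0 in the model as written. The three-way coefficient in the fuller model is 0.

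**3. Chance imbalance at baseline.** The standard error of the baseline arm-by-ethnicity contrast is SD × √(2/113 + 2/57) = SD × 0.230. This is 1.93 kg/m2 for parents and 1.47 points for children. The standard error of the named term over all four visits is 1.91 and 1.37, so repeated measurement reduces it very little.

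**4. The 18-month contrast of change, visits as categories.** SE = SD × √(2(1 − ρ³)) × 0.230.
- Parents: 8.4 × √(2 × 0.0297) × 0.230 = 0.47. For D = 1.0, 1.0/0.47 = 2.13, power 57%.
- Children: 6.4 × √(2 × 0.271) × 0.230 = 1.08. For D = 3, 3/1.08 = 2.77, power 79%.

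**5. Named term against three-way term, linear time and a linear differential.**

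| Outcome | D | Named term: expected value (SE) | Power | Three-way SE | Power |
|---|---|---|---|---|---|
| Parents' BMI | 1.0 | 0.50 (1.91) | 6% | 0.44 | 63% |
| | 1.5 | 0.75 (1.91) | 7% | 0.44 | 93% |
| | 2.0 | 1.00 (1.91) | 8% | 0.44 | 99.6% |
| Child percentile | 2 | 0.99 (1.37) | 11% | 1.01 | 51% |
| | 3 | 1.48 (1.37) | 19% | 1.01 | 84% |
| | 4 | 1.97 (1.37) | 30% | 1.01 | 98% |

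The named term absorbs about half of D. A random intercept and slope covariance gives nearly the same results.

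**6. Differential present by 3 months and constant afterwards.** Over the same values of D and both covariances, the named term has power 6-12% for parents and 13-60% for children. A linear three-way term also loses power here: 17-37% for parents at D = 1.0 and 31-57% for children at D = 3, against 6-7% and 22-38% for the named term. The contrast in step 4 does not depend on the path and keeps its 57% and 79%.

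**7. Group-specific SDs.** With Table 3's child SDs of 6.4 (African American) and 8.1 (white), √(2 × 6.4²/113 + 2 × 8.1²/57) = 1.74. Then SE = 0.736 × 1.74 = 1.28, and power for 3 points in step 4 is 65% instead of 79%.

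**8. Hispanic versus white.** 5% of 358 is about 18 dyads. The 95% half-width is 1.96 × SD × √(2(1 − ρ³)) × √(2/9 + 2/57), about 2.0 kg/m2 and 4.7 points. With group-specific SDs (5.2 and 8.2 for parents, 5.2 and 8.1 for children) it is about 1.4 kg/m2 and 4.2 points.

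**The case against.** The best defence is that arm-by-time is not written in Aim 1. If Aim 1 analysed only post-baseline visits conditional on the baseline outcome, arm-by-ethnicity would be a valid average differential effect. Two things lend this some support: the Aim 2 models, said to be structured like those of Aim 1, carry a baseline covariate, and characteristics that differ at baseline are to be adjusted for. The premise is therefore an inference, though a strong one. The baseline covariate is stated for Aim 2 alone, the power models use all time points, and the adjustment rule concerns overall differences between arms, not differences within ethnicity.

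A second defence is that a condensed article leaves term lists to the full plan. That would excuse silence. Here the article names the interactions and their order, and that wording can be judged. It cannot be concluded that no fuller model exists elsewhere.

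A reader might infer that the named term is blind to differential benefit. It is not: it picks up about half of a linear differential, and power in children can reach 60% when the differential appears early and persists.

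A reader might also infer that the Hispanic comparison should go untested. The article reports the 5% openly, and its aim covers three groups. Dropping the comparison is a preference and would leave part of the aim unanswered.

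The power figures rest on assumed differentials and ignore the stated intracluster correlation of 0.01 and dropout. Exact values move with these choices, as steps 6 and 7 show.

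**Conclusion.** The point stands as a mismatch between the terms named and the aim stated. On a literal reading, with arm-by-time as the inferred Aim 1 effect, the arm-by-ethnicity coefficient measures level with baseline included. It is open to chance imbalance, attenuated by about half under a linear differential, and weak. For African American versus white, power is about 6% against 57-63% for parents' BMI at 1.0 kg/m2, and about 19% against 79-84% for child percentile at 3 points. The lower figure in each range treats visits as categories and the higher uses linear time. The differentials are assumptions, and so are the 5% test, complete data and independence between clusters. The gain is smaller if the differential appears early and time is modelled as linear.

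Severity is moderate. The aim is exploratory, and the primary outcomes and the Aim 1 comparison are not affected.

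**What to change.** Replace the pairwise test with arm-by-time-by-ethnicity terms. Keep every lower-order term, including ethnicity-by-time. Define differential benefit as the difference between ethnic groups in the arm contrast of change from baseline to 18 months. Estimating that contrast with visits as categories avoids dependence on a linear path.

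An acceptable alternative is to model only post-baseline visits conditional on the baseline outcome and say so. Arm-by-ethnicity is then an average differential effect over follow-up.

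Keep the Hispanic contrast, reported as an estimate with its confidence interval and a note that it rests on about 18 dyads.

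The cost is a sentence or two of wording and a few more model parameters. Data collection does not change.

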### Sample characteristics

Baseline characteristics of parents and children are summarized in Table 2. The mean age of the parents was 36.7 years and the great majority were female (93%). Over half (63%) of the parents and children were African American, 32% were non-Hispanic white, and 5% bilingual Hispanic. The mean age of the children was 8.6 years and the majority (56%) was also female.

**Table 2 T2:** Demographic Characteristics of Parents and Children

**Parents****(*n *= 358)**	
Age	36.7 (+/- 8.0) years
Gender	
Female	93%
Male	7%
Ethnicity and Race	
African American	63%
Non-Hispanic White	32%
Bilingual Hispanic	5%
Education	
< 6 grade or less	1%
Middle School	8%
High School or GED	35%
Associates Degree	44%
Baccalaureate Degree	8%
Graduate Degree	4%
Children (*n *= 358)	
Age	8.6 (+/- 1.0) years
Gender	
Female	56%
Male	44%
Ethnicity and Race	
African American	63%
Non-Hispanic White	32%
Bilingual Hispanic	5%
Education	
2^nd ^grade	20%
3^rd ^grade	41%
4^th ^grade	39%
Birth Order	
1^st ^born	43%
2^nd ^born	34%
3^rd ^born	15%
4^th ^born	6%
5^th ^born	2%

The parents' mean BMI was 37.6, which is classified as obese (Table 3). African American parents mean BMI (38.4) was higher than either non-Hispanic white parents' (36.3) or Hispanic parents' BMIs (32.8). The children's mean BMI percentile was 95.2%, which is also classified as obese. African American children (95.5%) and Hispanic children (95.2%) were similar but non-Hispanic white children (94.0%) were lower.

**Table 3 T3:** Weight and adiposity by total sample and by ethnicity of parents and children

Variable	Mean (+/-SD)		Mean (+/-SD)
**Total Parents (*n *= 358)**		**Total Children (*n *= 358)**	
Height	163.9 (+/- 6.6) cm	Height	138.8 (+/- 8.5) cm
Weight	101.2 (+/- 24.2) kg	Weight	49.1 (+/- 14.1) kg
Body Mass Index	37.6 (+/- 8.4)	Body Mass Percentile	95.2 (+/- 6.4)
Waist Circumference	109.4 (+/- 18.4) cm	Waist Circumference	77.5 (+/- 13.6) cm
Subscapular Skinfolds	37.0 (+/- 9.9) mm	Subscapular Skinfolds	22.4 (+/- 10.4) mm
Triceps Skinfolds	37.3 (+/- 10.4) mm	Triceps Skinfolds	24.7 (+/- 8.9) mm
African American Parents		African American Children	
Body Mass Index	38.4 (+/- 8.4)	Body Mass Index Percentile	95.5 (+/- 6.4)
Waist Circumference	111.2 (+/- 17.9) cm	Waist Circumference	78.0 (+/- 13.7) cm
Subscapular Skinfolds	38.6 (+/- 9.9) mm	Subscapular Skinfolds	22.9 (+/- 10.5) mm
Triceps Skinfolds	39.4 (+/- 10.4) mm	Triceps Skinfolds	25.4 (+/- 9.5) mm
Non-Hispanic White Parents		Non-Hispanic White Children	
Body Mass Index	36.3 (+/- 8.2)	Body Mass Index Percentile	94.0 (+/- 8.1)
Waist Circumference	106.5 (+/- 19.0) cm	Waist Circumference	76.4 (+/- 13.5) cm
Subscapular Skinfolds	34.6 (+/- 9.5) mm	Subscapular Skinfolds	21.7 (+/- 10.5) mm
Triceps Skinfolds	36.3 (+/- 8.2) mm	Triceps Skinfolds	23.5 (+/- 8.0) mm
Hispanic Parents		Hispanic Children	
Body Mass Index	32.8 (+/- 5.2)	Body Mass Percentile	95.2 (+/- 5.2)
Waist Circumference	99.6 (+/- 12.1) cm	Waist Circumference	76.6 (+/- 11.0) cm
Subscapular Skinfolds	30.6 (+/- 7.5) mm	Subscapular Skinfolds	19.1 (+/- 6.0) mm
Triceps Skinfolds	30.2 (+/- 9.6) mm	Triceps Skinfolds	23.3 (+/- 6.7) mm

Parents' mean waist circumference was 109.4 cm, which is classified as obese. African American parents (111.2 cm) had higher waist circumferences than non-Hispanic white (106.5 cm) and Hispanic parents (99.6 cm). Parents' mean subscapular skinfolds were 37.0 mm and triceps skinfolds were 37.3 mm, which are both classified as obese. Again, African American parents had higher subscapular (38.6 mm) and triceps skinfolds (39.4 mm) than non-Hispanic white (34.6 mm; 36.3 mm) and Hispanic parents (30.6 mm; 30.2 mm). The children's mean waist circumference was 77.5 cm, which is classified as obese. African American children (78.0 cm) had higher waist circumferences than non-Hispanic white (76.4 cm) and Hispanic children (76.6 cm). The children's subscapular skinfolds were 22.4 mm, and triceps skinfolds were 24.7 mm, both classified as obese. Again, African American children had higher subscapular skinfolds (22.9 mm) and triceps skinfolds (25.4 mm) than non-Hispanic white children (21.7 mm; 23.5 mm) and Hispanic children (19.1 mm; 23.3 mm).

Health behavior outcomes were measured in children using the Child and Adolescent Trial for Cardiovascular Health (CATCH) [55] questionnaire and the Child Health Behavior Survey [53]. On the CATCH mean scores for dietary intention (1.5), usual food choices (1.5), dietary knowledge (1.5), dietary habits (1.4), and support for physical activity (1.4) were moderate. In addition, children reported support for making healthy food choices from parents (1.4), teachers (1.5) and friends (1.6) (See Table 4).

**Table 4 T4:** CATCH health behavior questionnaire

Variable	Mean (SD)
Dietary Intention	1.5 (+/- 0.13)
Usual Food Choices	1.5 (+/- 0.13)
Dietary Knowledge	1.5 (+/- 0.11)
Dietary Habits	1.4 (+/- 0.16)
Support for	1.4 (+/- 0.15)
Physical Activity	
Food Choices(Parent Support)	1.4 (+/- 0.26)
Food Choices(Teacher Support)	1.5 (+/- 0.31)
Food Choices(Friend Support)	1.6 (+/- 0.31)
Diet Self-Efficacy	2.3 (+/- 0.47)
Physical Activity Self-Efficacy	2.5 (+/- 0.45)

The Child Health Behavior Survey [53] measures usual daily and weekly food and beverage intake and found that 52% of the children drank 2 or more sweetened beverages a day, 21% drank 3 or more glasses of milk a day and 45% drank water when thirsty. Eleven percent ate 4 or more vegetable servings a day and 20% had 4 or more servings of fruit a day. When having a snack 46% chose candy, chips, cereals, cookies or cake and 44% chose fruit, vegetables, yogurt or ice cream for a snack (Table 5).

**Table 5 T5:** Child health behavior survey

Variable	Category	Percent
Sweetened Beverages	None	11.7%
	< 1 glass	11.5%
	1 glass	19.5%
	2 glasses	22.6%
	3 glasses	15.6%
	4 or more glasses	13.7%
	Don't Know	5.3%
Milk	None	17.0%
	< 1 glass	10.6%
	1 glass	27.9%
	2 glasses	22.4%
	3 glasses	8.4%
	4 or more glasses	12.3%
	Don't Know	1.4%
Usually Drink	Unsweetened	5.9%
	Juice	26.6%
	Milk	6.2%
	Sweetened drink	9.2%
	Sports drink	5.6%
	Water	44.8%
	Don't know	1.7%
Vegetables	None	12.3%
	< 1 serving	5.0%
	1 serving	28.6%
	2 servings	23.3%
	3 servings	15.9%
	4 or more serving	11.2%
	Don't Know	3.6%
Fruit	None	7.3%
	< 1 serving	5.6%
	1 serving	22.4%
	2 servings	25.1%
	3 servings	16.2%
	4 or more serving	20.4%
	Don't Know	3.1%
Snacks	Candy	6.2%
	Chips	18.9%
	Cereal	7.8%
	Cookies or Cake	13.4%
	Fruit	30.5%
	Vegetables	4.2%
	Yogurt or Ice Cream	8.9%
	Other Snack	10.0%

Health behavior outcomes were measured in parents using the Adult Health Behavior Survey [53] and The Health Promoting Lifestyle Profile II [54]. The Adult Health Behavior Survey [53] measures daily and weekly food and beverage intake. Over 50% of the parents drank 2 or more sweetened beverages a day, 4% drank 3 or more glasses of milk a day and 46% drank water when thirsty. Six percent ate 4 or more servings of vegetables a day and 3% ate 4 or more servings of fruit a day. When having a snack 61% chose candy, chips, cereal, cookies or cake and 22% chose fruit, vegetables, yogurt or ice cream (Table 6).

**Table 6 T6:** Adult health behavior survey

Variable	Category	Percent
Sweetened Beverages	None	18.7%
	< 1 glass	13.9%
	1 glass	15.4%
	2 glasses	21.8%
	3 glasses	14.8%
	4 or more glasses	13.7%
	Don't Know	1.7%
Milk	None	35.8%
	< 1 glass	20.9%
	1 glass	25.7%
	2 glasses	11.5%
	3 glasses	3.6%
	4 or more glasses	0.6%
	Don't Know	1.9%
Usual Drink	Unsweetened	11.5%
	Juice	6.7%
	Milk	0.6%
	Sweetened Drink	29.9%
	Sports Drink	3.9%
	Water	46.1%
	Don't Know	1.4%
Vegetables	None	1.1%
	< 1 serving	7.5%
	1 serving	22.4%
	2 servings	42.5%
	3 servings	19.6%
	4 or more serving	6.2%
	Don't Know	0.8%
Fruit	None	9.5%
	< 1 serving	17.9%
	1 serving	30.5%
	2 servings	25.7%
	3 servings	11.7%
	4 or more serving	2.5%
	Don't know	2.2%
Snacks	Candy	3.9%
	Chips	28.2%
	Cereal	12.9%
	Cookies or Cake	15.9%
	Fruit	8.4%
	Vegetables	2.8%
	Yogurt or Ice Cream	11.2%
	Other Snack	13.1%

The Health Promoting Lifestyle Profile II examines health responsibility, nutrition, exercise, and stress (Table 7). On the subscales the parents mean score for health responsibility (1.3) was sometimes, nutrition (2.2) was often, exercise (0.9) was never to sometimes and stress (1.3) was sometimes.

**Table 7 T7:** Health promoting lifestyle profile II, eating self-efficacy and exercise self-efficacy

	Variable	Total Mean (SD)
HPLPII	Health Responsibility	1.3 (+/- 0.56)
	Nutrition	2.2 (+/- 0.49)
	Exercise	0.9 (+/- 0.56)
	Stress	1.3 (+/- 0.50)

Exercise	Self-Efficacy	45.0 (+/- 21.9)

Eating	Self-Efficacy^1^	
	Negative Affect	43.6 (+/- 21.5)
	Socially Acceptable	37.5 (+/- 13.1)
	Total Scale	80.8 (+/- 31.1)

Eating	Self Efficacy^2^	
	Most difficulty controlling eating	0.22 (+/- 0.49)

Eating Self Efficacy Scale^1^: rescaling 6 to 6.5 for the cohorts received 1 to 6 scale instrument

Eating Self Efficacy Scale^2^: proportion of most difficulty controlling eating (6 & 7)

Self-efficacy in children was measured using the CATCH [55] questionnaire, which examines diet self-efficacy (2.3) and exercise self-efficacy (2.5) (Table 4). Self-efficacy in parents was measured using the Eating Self-Efficacy Scale [56] and the Exercise Self-Efficacy Scale [33]. See Table 7. The children had moderate mean scores on diet self-efficacy (2.3) and physical activity self-efficacy (2.5). The parents demonstrated moderate scores in eating self-efficacy for the negative affect scale (43.6) and socially acceptable scale (37.5). In exercise self-efficacy the parents scored moderately (45.0) on the scale.

